# Efficacy and Usability of eHealth Technologies in Stroke Survivors for Prevention of a New Stroke and Improvement of Self-Management: Phase III Randomized Control Trial

**DOI:** 10.3390/mps2020050

**Published:** 2019-06-13

**Keywords:** stroke, rehabilitation, self-management, quality of life, eHealth, decision support system, prevention

## Abstract

Background: Stroke is a leading cause of severe and long-term disability in developed countries. Around 15 million people suffer a stroke each year, being most of them ischemic due to modifiable risk factors. Adequate self-management abilities may help to manage the consequences of stroke, but it is unknown which specific intervention could be effective to booster these self-management abilities. Objective: To evaluate the improvement of self-management in chronic stroke survivors using decision support and self-management system (STARR). Methods: A randomized, prospective, parallel group, open, and the unicentric pilot trial will be performed. Stroke survivors and their caregivers will be randomly allocated to STARR management or standard of care. Main inclusion criteria are mild to moderate disabled first stroke adult survivor, living at home, able to cope and follow the guidelines and devices, without socio-familial exclusion. All will get a conventional treatment in the acute and subacute phase; however, in the chronic period, cases will use the developed STARR App and Decision Support System. Measurements will be performed at baseline, at 3 months, and at 6 months. Outcome measures are patient-report outcome measure of self-management competency, physical function, risk factor reduction, healthcare resource utilization, knowledge of the condition, mood, and social isolation. Discussion: If effective, the results of this study will enable stroke patients and their caregivers to deal better with the everyday life obstacles of stroke, improve the adherence of the treatment, improve the control of cardiovascular risk, and, in consequence, reduce the recurrence of secondary strokes, the number of complications, the number of consultations, and readmissions; to ultimately reduce the health systems costs. Taking into consideration that the number of stroke survivors is increasing around the world, a large number of individuals could profit from this intervention.

## 1. Background

Stroke is a leading cause of severe and long-term disability in developed countries, having an estimated total cost of approximately €64 billion per year in Europe for 2010 [1]. Around 15 million people suffer a stroke each year; [2] most of them being ischemic due to modifiable risk factors, such as hypertension, diabetes, obesity, dyslipidemia, smoking, alcohol consumption, sedentary life, and unhealthy diet [3]. Moreover, the number of persons having a stroke in Europe is likely to increase from 1.1 million per year in 2000 to more than 1.5 million per year in 2025, solely because of the aging population [4]. One-third of the people going through a stroke die. Thus, in Europe, there are around 650,000 stroke deaths each year [5]. One-third of the people who have suffered a stroke are left permanently disabled, with complications, including motor, cognitive, and language impairments, as well as psychological problems [6]. Estimates indicate that more than one-third of the patients still require assistance for daily living activities 6-years post-stroke [7]. It is well known that recurrent or secondary stroke carries with it a greater risk than the first-ever stroke for death and disability [8,9,10]. Fortunately, thanks to the new medical and technological advances in the treatment of acute stroke (e.g., mechanical thrombectomy and intravenous fibrinolysis), the mortality from the first stroke has decreased over the past years. However, consequently, the number of people at risk for a secondary stroke has increased, with an associated increase in healthcare costs [11]. In the US, from 1995–2005, the stroke death rate fell approximately 30%, and the actual number of stroke deaths declined approximately 14% according to U.S. Centers for Disease Control and Prevention [12]. It has been generally acknowledged for years that nonadherence rates for chronic illness regimens and for lifestyle changes are around 50%, even though the success of the medical treatment is largely determined by adherence. Adherence in long-term conditions can be improved by self-management interventions [13,14]. To ease and improve self-management conditions, there has been a boost for new technology-based intervention, which has mostly been studied in diabetes, asthma, and hypertension [15,16,17,18]. The use of mobile phone messaging, such as short message service and multimedia message service, has been used, as well as smartphones and tablets in telemedicine [15]. The prevention of stroke has been studied in some papers that propose different strategies for reducing cerebro-cardiovascular risk factors. Among these strategies, there is evidence for a phone-based computer aided prevention system [19] and an individualized coaching program executed by well-trained stroke nurses [20]. Several reviews have shown that interventions mediating the new eHealth technologies can reduce the risk of suffering a stroke episode, improving the control of risk factors; nevertheless, all of them conclude that new and well-designed studies are needed [15,21]. Therefore, in this study, we propose the development of a mobile phone/tablet application to be used at the patient’s home, which acts as a coach for the patient and the caregiver providing recommendations for lifestyles and medical treatments based on evidence, which are related to the risk of a new stroke episode.

## 2. Methods/Design

### 2.1. Primary Objective

The aim of the study is to evaluate the improvement of self-management at home in chronic stroke survivors using the decision support and self-management system for stroke survivors (STARR) (compared with standard of care). Improving the self-management means increasing physical function, controlling risk factors for a new cardiovascular event, improving quality of life, as well as other items, such as self-management behaviors, adherence to treatments indicated by the doctor, improving health care resource utilization, knowledge of the condition, mood, and social isolation. The alternative hypothesis would be that STARR management improves self-management, as well as the quality of life of stroke survivors.

### 2.2. Secondary Objectives

Improvement of the study participants’:Self-management.Level of independence in the activities of daily living (ADL).Quality of life.Adherence to home-based rehabilitation and pharmacological and non-pharmacological treatment.Need for caregivers (family, care providers…).Recurrent stroke and the complications related to stroke.A number of hospital readmissions, emergency care, and outpatient visits to the hospital and primary care centers.

Also, the study will evaluate:Cost-effectiveness of the developed system.Accessibility of the developed system.Sustainability of the developed system.User’s satisfaction (by users, we mean stroke survivors, caregivers, and professionals using the developed system).Possible adverse events that the system can cause on the study participants.

In addition, the efforts will be made to identify new variables related to the prognosis of stroke.

### 2.3. Participants

Inclusion criteria age 18 years to 80 years;having a diagnosis of first ischemic stroke within the past 6 months;hemiparesis with mild (91-99) or moderate (61-90) disability (Barthel Index, BI);with or without speech pathology but able to understand simple orders (Mississippi Aphasia Screening Test, >45);able to cope and to understand the guidelines to use the devices;the life expectancy of at least 12 months;no severe cognitive impairments (Montreal Cognitive Assessment, MoCA, >26);without medical comorbidities that could interfere with the home-rehabilitation program (for example, severe aortic stenosis, respiratory failure, severe osteoarthrosis);without socio-familiar dystocia (Gijon’s socio-familial evaluation scale (SFES) <14)without a basal functional situation >1 by a Modified Rankin Scale (MRS).

Exclusion criteriamedical comorbidities that could interfere with the home-rehabilitation program.refusal to sign the informed consent and participate in the study.

### 2.4. Study Design

We will perform a prospective, randomized, parallel group, open, and unicentric pilot trial. We will analyze the data from 40 patients between 18 and 80 years old who have had an ischemic stroke, and whose family or friend caregivers are followed at Rehabilitation Unit at Cruces University Hospital. Two groups will be formed. The control group will get conventional treatment from the acute to the chronic phase of stroke, and the intervention group will get a conventional treatment to the end of the subacute phase. However, in the chronic period, they will use the developed STARR System, as well as commercial wearables.

The main stages of stroke recovery are defined by temporal terms (acute, subacute, and chronic). The acute stage refers to the first 7-days-period of the stroke event. The subacute stage represents the patients from the first week till 6 months, dividing this period in two: early subacute (up to 3 months) and late subacute (from 3 to 6 months). The chronic stage is beyond 6 months when brain repair processes suggest that the majority of the recovery has occurred [22].

The STARR system is based on the following components:**Wearables and connected objects**: provide regular information about the evolution of certain risk factors (e.g., physical activity, blood pressure) without taking over users’ attention. The devices of the STARR system are composed of a tensiometer, a glucometer, a heart rate band, a balance, and a thermometer. All of them are commercial devices tested and with CE marking.**A decision support system (DSS)**: implements personalized advice, guidance, and follow-up for daily life activities of the stroke survivors by analyzing the information coming from the wearables and the connected objects, a number of predictive models, and user profiles. The DDS has a system of alarms that will guide patients in making decisions, with recommendations, such as modifying life habits, consulting with their general practitioner, or going to the emergency department. These alarms are based on clinical practice guidelines with proven evidence in the management of patients with stroke. In addition, the responsible doctor of the study participant will have access to a control panel in the health system and a mobile application, where the alarms of the patients can be managed.**Predictive models**: will be populated by risk assessment information provided by validated predictive models calculating stroke risk. The risk estimation done by these models will be complemented by information from a model of human motion analysis and guidance developed during the project using Kinect’s cameras and a created program algorithm, which has been found to be very useful for assuring continued engagement in physical activities in clinical and home settings. It will also be supported by the implementation of models of behavior change to capture individual variations and attitude changes over time. The key requirement behind the implementation of these models is to motivate self-management by encouraging self-awareness and trend-awareness in lifestyle in the sub-acute and chronic phases of stroke.**Self-management apps (DSS user interface)**: tools to inform and encourage stroke survivors to self-manage their condition. The STARR system will try to determine the user’s reason for non-adherence using a mobile phone app and an online lifestyle diary. The user will then automatically receive generated messages with persuasive, tailored content. The content will be different at different stages of the initiation and maintenance of health behavior.**Serious games**: promote physical activity and rehabilitation at home with suggested activities in serious games with a screen and a mini-bike.

The different components are currently being developed and will be adapted to fit specified scenarios and services.

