### 2.13. Sample Size

To obtain a power of 80% to detect statistically significant differences when comparing the null hypothesis—a bilateral chi-squared test for two independent samples—taking into account that the level of significance is 5% and assuming that the proportion of dependence in the control group is 41.5% [23] and the proportion in the intervention group is 15%, a total of 72 stroke survivors will be needed. Taking into account the expected percentage of dropouts of 10%, it will be necessary to recruit 80 patients. The dependence will be measured by SSSMQ and Family needs of stroke patient questionnaire.

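### Section 2.4 analyses 40 patients while section 2.13 requires 72 analysed and 80 recruited, and 72 does not give the stated 80% power under the two-sided test

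*Protocol article*

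**What the plan says.** Section 2.4 (Study Design) states: "We will analyze the data from 40 patients between 18 and 80 years old who have had an ischemic stroke". It then says "Two groups will be formed". Section 2.6 (Recruitment) fixes 1:1 allocation.

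Section 2.13 (Sample Size) opens with "To obtain a power of 80% to detect statistically significant differences" and names "a bilateral chi-squared test for two independent samples" at a 5% significance level. The assumed proportions with dependence are 41.5% in the control group and 15% in the intervention group. From these it derives 72 stroke survivors in total and continues: "Taking into account the expected percentage of dropouts of 10%, it will be necessary to recruit 80 patients".

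No interim look, subset or separate pilot stage of 40 patients is described, and 40 is nowhere called a per-group figure.

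**The concern.** The two sections give different values for the most basic design quantity. A reader cannot tell what the recruitment target is or, later, whether it was reached. If 40 is the true total, the power statement in 2.13 does not describe the trial that will be run. A non-significant result would then be at least as likely as a significant one even if the assumed 26.5-point effect were real. This matters because section 3 (Discussion) says a trial with 3–5 years of follow-up will be done if the 6-month results are positive.

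A further question is whether 72 and 80 are themselves right. If they are not, bringing 2.4 into line with 2.13 would remove the contradiction but leave a wrong power claim in place.

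**Working it through.** **Inputs, all from section 2.13 unless noted.** p1 = 0.415, p2 = 0.15, difference d = 0.265; two-sided 5% (z = 1.960); power 80% (z = 0.842); dropout 10%; 1:1 allocation (section 2.6); 40 analysed (section 2.4).

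**Building blocks.**
- Mean proportion: (0.415 + 0.15)/2 = 0.2825. Null term: √(2 × 0.2825 × 0.7175) = √0.4054 = 0.6367.
- Alternative term: √(0.415 × 0.585 + 0.15 × 0.85) = √(0.2428 + 0.1275) = √0.3703 = 0.6085.

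**Step 1: try to reproduce 72 and 80.** For the chi-squared test, n per arm = [(1.960 × 0.6367 + 0.842 × 0.6085)/0.265]² = (1.760/0.265)² = 44.1, so 45 per arm and 90 in total. The stated 72 is not reproduced. Other two-sided formulas do not reach it either: 84 (unpooled variance), 86 (arcsine), 104 (continuity correction). A one-sided 5% test (z = 1.645) gives (1.559/0.265)² = 34.6, so 35 per arm and 70 in total, close to 72. That would contradict the two-sided test the section names. The dropout step does reproduce: 72/0.9 = 80. Applied to 90 it gives 90/0.9 = 100 recruited.

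**Step 2: power at each candidate number.** Power = Φ[(0.265 × √n − 1.960 × 0.6367)/0.6085], with n per arm and 1.960 × 0.6367 = 1.248.
- n = 20: (1.185 − 1.248)/0.6085 = −0.103, giving 45.9%.
- n = 36: (1.590 − 1.248)/0.6085 = 0.562, giving 71.3%.
- n = 40: (1.676 − 1.248)/0.6085 = 0.704, giving 75.9%.

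**Step 3: check by exact enumeration and by method.** Section 2.14 allows chi-squared or Fisher, so both matter.

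| Analysed | Pooled formula | Arcsine | Unpooled | Exact, uncorrected chi-squared | Exact, Fisher |
|---|---|---|---|---|---|
| 40 | 45.9% | 48.1% | 49.5% | 48.1% | 35.4% |
| 72 | 71.3% | 72.7% | 74.3% | 72.6% | 63.3% |
| 80 | 75.9% | 77.1% | 78.7% | 76.7% | 69.1% |
| 90 | 80.8% | 81.8% | 83.2% | not run | not run |

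No two-sided method gives 80% at 72, or even at 80.

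**Step 4: precision.** 95% half-width = 1.960 × √(0.3703/n).
- n = 20: 1.960 × 0.1361 = 0.267, about ±27 points, as wide as the assumed effect of 26.5 points.
- n = 36: 1.960 × 0.1014 = 0.199, about ±20 points.

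**The case against.** The strongest reply is that 40 is exactly half of 80, with two groups and 1:1 allocation, so the words *per group* may simply have been dropped. This is plausible, and if it is what was meant, no power is lost relative to 2.13 and the repair to 2.4 is a few words. Two things still stand. The text does not say it. And 2.4 speaks of patients analysed, whereas 80 is the number recruited; after the 10% dropout allowed in 2.13, 72 would be analysed, which is 36 per group and not 40. Section 2.4 needs correcting on either reading.

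A second reply is that the power figure covers only the planning endpoint. This stands as a limit. Section 2.13 powers a binary dependence outcome, while the primary outcome in 2.10 is questionnaire-based, and 2.14 compares continuous variables by t-test or Mann-Whitney. If questionnaire scores are analysed as continuous, 46% is not the power of that analysis. It is the right figure against which to judge the claim in 2.13.

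Some stronger readings are tempting but not supported:
- A reader might take a further 10% off the 40 for dropout. Section 2.4 calls the 40 analysed, so that deduction does not follow.
- A reader might infer that the longer trial hinges on p ≤ 0.05. The Discussion says only that results should be positive, and the 5% threshold in 2.14 is general.
- The title says "Phase III Randomized Control Trial" while 2.4 and 2.10 call the study a pilot. The label should be made consistent, but this is a side issue: it does not show which number was intended.

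**Conclusion.** The contradiction between 40 and 72/80 is certain on the text. The fall to about 46% power (roughly 46–50% across uncorrected methods, about 35% with Fisher) is conditional on 40 being the total. A reader might infer that the trial is definitely planned at 46% power; the article does not settle that.

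The second error does not depend on how 40 is read. With the inputs of 2.13 and its two-sided 5% test, 72 analysed gives about 71% power, and about 90 analysed (100 recruited) are needed for 80%. If 40 is the total, the real drop is therefore from about 71% to about 46%, and not from 80%. That 72 came from a one-sided calculation is a likely explanation, not something the article states.

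All power figures assume that the 41.5% and 15% rates are correct and that the comparison is the binary one in 2.13. The sample-size statement is wrong as written and should be corrected.

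**What to change.** State one sample size, giving both the recruited and the analysed number, in the same terms in sections 2.4 and 2.13, and say whether each figure is a total or per group. Then replace the 80% claim with the power and interval width which that number gives under the stated two-sided test:

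- 80 recruited, 72 analysed (36 per group): about 71% power, 95% half-width about ±20 points.
- 40 analysed in total (20 per group): about 46% power (about 35% if Fisher's test is used), half-width about ±27 points.

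Either version is a wording change in two sections and needs no extra patients. Changing 2.4 to 80 and leaving 2.13 untouched is not enough. If the sponsor wishes to keep 80% power with the two-sided test, the target becomes about 90 analysed and 100 recruited. That is 20 more than the present recruitment figure of 80, and a much larger increase at this single centre if 40 was the working target. The trial label in the title and in 2.4 and 2.10 can be made consistent in the same edit.

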### 2.5. Reason for Withdrawal From the Trial

Patients can withdraw from the study at any time and revoke informed consent, both stroke survivors and caregivers. In addition, they may be withdrawn if one of the following events occurs:DeathLoss of follow-upSevere disease of the principal caregiverAny other problems that, in the opinion of the research team, justify treatment withdrawal.

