### 2.10. Outcome Measures

The primary clinical focus in this pilot trial is the evaluation of self-management of the stroke survivors. The proposed primary outcome will be measured by the validated Southampton Stroke Self-Management Questionnaire (SSSMQ) and Family needs of stroke patient questionnaire.

A series of secondary outcomes will be evaluated at different time points, such as the effectiveness of stroke self-management interventions. They rely upon the following items:-Physical function (PF) assessed by the modified BI and Lawton index.-Risk factor reduction (blood pressure, analytical profile -glycemia, HbA1c, lipids, weight, heart rate control, medication compliance).-Self-management behaviors by self-reported information on lifestyles: diet assessed by the Mediterranean diet assessment tool, exercise assessed by tracking with the wearables, smoking, and alcohol consumption.-Healthcare resource utilization by the information available in the public health system in Osakidetza, Cruces university hospital.-Knowledge of condition to assess whether there is a relationship between health literacy and control of cardiovascular risk factors, number of complications, number of recurrences, low adherence to pharmacological and non-pharmacological treatment, and self-management behaviors.-Mood and social isolation by Goldberg scale that measures anxiety and depression.-Stroke Self-management questionnaire (SSMQ).

Other secondary outcomes will be focused on the International Consortium for Health Outcomes Measurement (ICHOM), such as survival, disease control, and acute complications.

All the questionnaires and measurements for the achievement of the outcomes will be collected through face-to-face medical visits in the neuro-rehabilitation department.

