### 2.12. Follow-up Period

All patients recruited for the research clinical trial (RCT) will be reassessed during external consultations at month 3 ± 1 week (1^st^ visit) and at month 6 ± 1 week (final visit).

All the participants will get the same reassessment at the event day (evaluation a), recruitment visit (evaluation b), 3 months later (evaluation c), and 6 months of follow-up (evaluation d) taking into consideration that not all the tools are administered at each time.

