### 2.14. Statistical Analysis

Each variable will be characterized using frequency distributions central tendency, such as the mean and median, and to determine variability standard deviation or the interquartile range according to its distributional characteristics.

Comparisons between groups and intra-groups will be performed using parametric tests provided that the distributional characteristics of the data meet the requirements; otherwise, non-parametric tests will be used.

Comparisons between two continuous variables will be performed using the Pearson or Spearman correlation, depending on the distributional characteristics.

The comparison of proportions between categorical variables will be carried out by means of a chi-squared test or its corresponding Fisher correction. The continuous variables will be compared using the comparison of the means (t-student test or ANOVA) if the sample distribution is normal, and if the distribution is not normal, then the non-parametric Mann-Whitney U test will be utilized.

The populations will be analyzed by intention to treat analysis and as stated in the protocol.

A micro-data collection form will be developed. The analysis of costs will be done from the perspective of the health system and direct costs. The data collected will serve to estimate the actual cost of procedure data under usual practice conditions and costs derived from the implementation of the new intervention in the different contexts under study.

The collection of these data, together with data on effectiveness and utility, will enable subsequent studies on economic analysis and cost-effectiveness/utility to help decision-making on which alternatives are most effective and efficient from the point of view of the health system.

The SPSS 23.0 program for Windows (SPSS Inc, Chicago, IL, USA) will be used. A p-value of 5% or lower is considered to be statistically significant. The statistical analysis will be blind to the intervention group.

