### 2.15. Quality Control and Assurance

For ensuring the quality of the study, data will be collected on the adherence to the intervention, the inclusion, and follow-up of all patients, as well as monitoring and quality of data entry.

If there were to be suspicion of a serious violation of the trial protocol, it would imply a significant effect on:(a)the physical or psychological integrity or safety of patients during the trial, or(b)the values of the study. The study sponsor will be contacted as soon as possible. In any case, all violations will be notified to the relevant authorities in accordance with current legislation.

The protocol will not be modified without the consent of the principal investigator and the sponsor. Any modification of the protocol requires Ethics Committee approval prior to its implementation except to avoid immediate risks in patients.

The study documents will be reviewed, comparing them to the originals. The researcher will be informed of the progress of the study, and the suitability of the facilities will be evaluated on an ongoing basis.

In addition, the study may be evaluated by internal auditors of the sponsor and inspectors designated by health authorities who will be allowed access to the database, original documents, and other study files. Audit reports by the sponsor will be kept confidential.

The current legislation will comply with the terms of protecting the confidentiality of data (Regulation UE 2016/679). For this, each patient will receive an alphanumeric identification code in the study that will not include any data that allows their personal identification. The principal investigator will have an independent list that will allow the connection of the identification codes of the patients participating in the study with the clinical and personal data. This list will never leave the center. Only the researchers responsible for the study and listed in the clinical protocol approved by the Ethics Committee, as well as the competent authorities, will have access to the study data.

The trial sponsor and the researchers of the study declare his or her willingness to make the results of the trial public, preferably through scientific means of dissemination, that is, publications submitted to the peer review process.

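### Section 2.5 makes caregiver illness and team-judged reasons to stop treatment into reasons to leave the trial, which permits discretionary loss of outcomes and conflicts with intention to treat.

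*Protocol article*

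**What the plan says.** Section 2.5 of the protocol article is headed as a list of reasons for withdrawal from the trial. Besides the right to revoke consent, it says of participants that "they may be withdrawn if one of the following events occurs". The events are death, loss to follow-up, severe disease of the principal caregiver, and any "other problems that, in the opinion of the research team, justify treatment withdrawal". The last item speaks of stopping treatment, although the section is about leaving the trial. No ground is limited to one arm.

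Four other places bear on this:

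- Section 2.4 describes a "prospective, randomized, parallel group, open, and unicentric pilot trial".
- Section 2.12 states: "All patients recruited for the research clinical trial (RCT) will be reassessed during external consultations at month 3" and again at month 6. These are months 9 and 12 after the stroke in Table 1.
- Section 2.14 states: "The populations will be analyzed by intention to treat analysis and as stated in the protocol". It adds: "The statistical analysis will be blind to the intervention group".
- Section 2.15 says that "data will be collected on the adherence to the intervention, the inclusion, and follow-up of all patients".

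On the outcome, section 2.10 says: "The proposed primary outcome will be measured by the validated Southampton Stroke Self-Management Questionnaire (SSSMQ) and Family needs of stroke patient questionnaire". Table 1 lists the SSSMQ as a patient measure, and Table 2 lists the family needs questionnaire as a caregiver measure.

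**The concern.** Intention to treat needs outcomes, as far as they can be obtained, on everyone randomised, in the arm assigned. A rule that lets the team end a patient's participation after randomisation, on open-ended grounds and with the arm known, works against that. Two of the grounds do not by themselves prevent measurement. A patient whose treatment has stopped can still attend the month 9 and month 12 visits, and a patient whose caregiver falls ill can still complete the SSSMQ.

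There is reason to think that such losses could differ between arms. Section 2.9 trains caregivers on the devices and sends them alarms, so caregiver illness may disrupt STARR use more than standard care. Sections 2.16 and 3 foresee that some patients will find the system hard to adapt to or will adhere poorly. If withdrawals in one arm were related to outcome, the analysis labelled intention to treat would move towards a completers' analysis. Blinding the statistician does not cure this, because the decision to withdraw comes earlier. Nor can an analysis plan recover visits that were never made.

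**Working it through.** **Passages side by side.** Under 2.12 every recruited patient is reassessed at months 3 and 6 after baseline, and under 2.14 everyone is analysed by intention to treat. Under 2.5 a recruited patient may be withdrawn from the trial because treatment should stop or the caregiver is ill. If withdrawal from the trial has its ordinary meaning, such a patient is not reassessed, and both statements cannot hold for that patient. If it means only stopping STARR, they can, but 2.5 does not say so.

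**The plan's own figure.** Section 2.13 allows 10% dropout: 72 / (1 − 0.10) = 80, which reproduces. The allowance is 80 − 72 = 8 patients. Section 2.4 instead speaks of 40 patients, and 10% of 40 is 4. Allocation is 1:1 (section 2.6), so the arms are 40 or 20.

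**Illustration on a continuous score.** If a fraction p of an arm is missing and those patients score d below the rest, the full-arm mean lies p × d below the completers' mean. The net bias in the difference between arms is (p_STARR − p_control) × d when d is the same in both arms. The documents give neither p by arm nor d. I assume d = 0.5 to 1.0 SD.

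| Split of 8 dropouts, 40 per arm | p_STARR | p_control | Net bias |
|---|---|---|---|
| 8:0 | 0.20 | 0 | 0.10 to 0.20 SD |
| 6:2 | 0.15 | 0.05 | 0.05 to 0.10 SD |
| 4:4 | 0.10 | 0.10 | 0 |

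With 20 per arm, a 4:0 split also gives p = 4/20 = 0.20 and the same 0.10 to 0.20 SD.

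For scale, the standard error of the difference in the extreme split is:

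- 32 against 40 patients: √(1/32 + 1/40) = 0.237 SD, so the bias is 0.10/0.237 = 42% to 0.20/0.237 = 84% of one standard error.
- 16 against 20 patients: √(1/16 + 1/20) = 0.335 SD, so the bias is 30% to 60% of one standard error.

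**Illustration on the planning scale.** Section 2.13 assumes 41.5% dependence in controls and 15% under STARR, a difference of 26.5 points. Suppose there is no true effect, both arms have 41.5% dependence (16.6 of 40), and every withdrawn patient is a dependent STARR patient.

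- 4 withdrawn: (16.6 − 4)/36 = 35.0%, a spurious difference of 6.5 points. By the normal approximation, a two-sided 5% test rejects about 9% of the time.
- 8 withdrawn: (16.6 − 8)/32 = 26.9%, a spurious difference of 14.6 points and rejection about 25% of the time.

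Both are adverse extremes, not forecasts. If the losses fell mainly in the control arm, or among patients doing well under STARR, the sign would reverse.

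**The case against.** A reader might infer that section 2.5 removes outcome data selectively, defeats intention to treat, and biases the result towards STARR. The documents do not support that.

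- The wording is permissive: patients may be withdrawn. Nothing says that their data are discarded, that visits stop, or that they leave the intention-to-treat set. Sections 2.12 and 2.15 point towards follow-up of everyone.
- The grounds apply to both arms. Controls also have scheduled exercises and guidance (section 2.8), and caregiver illness can occur in either arm.
- Difficulty with the devices is not a listed ground. Section 2.9 provides training, telephone support and home visits by a technician to keep such patients going.
- The caregiver ground has a rationale. Patients without a caregiver are not included (section 2.6), and one part of the primary outcome is a caregiver questionnaire, which severe illness may make unobtainable.
- Listing death as a withdrawal does not stop it being counted, since survival is a secondary outcome in section 2.10.
- The 10% allowance covers all dropout, including death, true loss and revoked consent, which no rewording would recover.
- Handling of missing data may sit in the full protocol or analysis plan, which are not shown.

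All of this stands, and it limits the claim. It does not remove the conflict. Section 2.5 is a printed rule, not an omission, and it puts a treatment-stopping reason under a trial-withdrawal heading. That sections 2.12 and 2.15 point the other way shows that the passages need to be reconciled.

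**Conclusion.** The point holds as a conflict in the stated rules and an avoidable risk, not as a demonstrated bias. In an open trial, section 2.5 permits discretionary and possibly arm-dependent loss of outcomes, at odds with sections 2.12 and 2.14. Size and direction are unknown. The 0.10 to 0.20 SD figure rests on two assumptions: that all planned dropout falls in the STARR arm, and that those patients score 0.5 to 1.0 SD worse. Even then it stays below one standard error of the difference. More balanced splits shrink it to zero. The amendment is worth making because it is cheap and matches what sections 2.12 and 2.15 already appear to intend.

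**What to change.** Amend section 2.5 to distinguish stopping the STARR intervention from leaving follow-up, and reconcile it with sections 2.12 and 2.14:

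- Unless the patient dies, is truly lost or revokes consent, collect the SSSMQ and the other scheduled patient measures at months 9 and 12 after the stroke, whatever the use of STARR or the caregiver's status.
- Collect the caregiver questionnaire where it can be obtained.
- Analyse each patient in the arm assigned.

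When treatment stops remains the clinicians' decision and is untouched. The cost is a wording amendment with ethics committee approval (section 2.15) and some extra effort to follow patients who no longer use the system. The visits are already scheduled.
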